##### UX and Usability Evaluation

The ITA BUS B [36] is a tool designed to evaluate the ease of use, effectiveness, and user satisfaction in interacting with the chatbot. While it is commonly used with artificial intelligence (AI)–powered chatbots, it is also applicable to other types of chatbot systems [36,40,41]. The 11 items are rated on a 5-point Likert scale, where 1 means “strongly disagree” and 5 means “strongly agree,” resulting in a total score ranging from 11 to 55. The areas investigated are as follows: perceived accessibility to chatbot functions, perceived quality of chatbot, perceived quality of conversation and information provided, perceived privacy and security, and time response.

SUS [35] is a quick and reliable tool for evaluating the usability of systems. Consisting of 10 items with Likert-type answers from 1 (“strongly agree”) to 5 (“strongly disagree”), the questionnaire provides a global score that reflects the ease of use and applicability of a system or product. The SUS yields a single number representing a composite measure of the overall usability of the system being studied, with a global score that can range from 0 to 100, depending on the degree of agreement with sentences such as “I found the system very cumbersome to use.”

UES-SF [34] measures user engagement with digital technology. Consisting of 12 items, the scale offers a quick but practical assessment of user engagement. Each item is rated on a 5-point Likert scale ranging from 1 (“strongly disagree”) to 5 (“strongly agree”), yielding a total score between 12 and 60. The questionnaire consists of four factors: (1) focused attention, which indicates the feeling of being immersed in the interaction; (2) perceived usability, which is the negative effect experienced due to the interaction and the effort expended; (3) aesthetic attractiveness, which represents the graphical and visual appeal of a digital solution; and (4) the reinforcement factor (reward). The latter is a single factor that includes duration, which evaluates the overall success of the interaction; novelty, which examines the general interest related to the interaction with a digital solution; and the perceived engagement factor, which evaluates the overall enjoyment of the interaction. As the questionnaire was not available in Italian, it was translated using the back-translation procedure. The 4 scales show good internal reliability, as follows: focused attention (ω=0.82), perceived usability (ω=0.86), aesthetic attraction (ω=0.84), and reinforcement (ω=0.81).

uMARS [37] is a tool for evaluating the quality of mobile apps. It provides a 20-item measure that includes 4 objective quality subscales—engagement, functionality, esthetics, and information quality—and 1 subjective quality subscale. One further subscale, consisting of 6 items, is added to measure users’ perceived impact of the evaluated app. This allows participants to obtain an in-depth and multidimensional evaluation of the quality of mobile apps. Each item offers answers on a Likert scale from 1 to 5, with 1 corresponding to “insufficient” and 5 to “excellent.”

##### Psychological Assessment

The Coping Orientation to Problems Experienced‐New Italian Version 25 (COPE-NVI-25) [42] is a shortened version of the Coping Orientation to Problems Experienced Inventory, designed to evaluate different coping strategies individuals use to deal with stress. This 25-item questionnaire explores strategies such as active coping, planning, and acceptance, providing a complex picture of an individual’s coping behavior. Specifically, 5 dimensions are examined: problem orientation, transcendent orientation, positive attitudes, social support, and avoidance strategies. These dimensions are assessed using a Likert scale ranging from 1 (“I never do it”) to 4 (“I often do it”), resulting in a total score between 25 and 100.

The Emotion Regulation Questionnaire [43] is a tool that evaluates 2 main emotion regulation strategies: expressive suppression and cognitive reappraisal. The questionnaire includes 10 items, with responses on a Likert scale from 1 (“strongly disagree”) to 7 (“strongly agree”), and is used to understand how individuals control and modify their emotional reactions in various contexts. On the basis of the answers, the score can vary from 10 to 70. Balzarotti et al [44] translated and validated the questionnaire in Italian, showing good psychometric characteristics.

GHQ-12 [39] is a self-assessment tool designed to identify mental health disorders and to monitor general psychological well-being. Because of its brevity, GHQ-12 has become one of the most widely used tools for detecting psychological distress. GHQ is widely used in clinical, research, and public health settings. The 12 items of the questionnaire are formulated to investigate how the individual has felt recently concerning psychological symptoms (such as anxiety and depression), ability to cope with daily situations, sleep disorders, and somatic symptoms. The response is based on a 4-point Likert scale, ranging from “not at all” to “much more than usual,” with a maximum score of 36.

The General Self-Efficacy Scale (GSE) [45] is a psychometric tool designed to evaluate an individual’s general perception of self-efficacy, that is, confidence in organizing and executing the actions necessary to manage potentially stressful or difficult situations. The GSE consists of 10 statements on which respondents must express their level of agreement on a Likert scale ranging from 1 (“not at all true”) to 4 (“exactly true”). The scale items explore various aspects of self-efficacy, such as the ability to solve problems, overcome obstacles, and handle unexpected situations. The total score, obtained by adding the scores of all the items, reflects the general level of self-efficacy perceived by the individual and can vary from 10 to 40, with a higher score indicating more self-efficacy.

K-10 [28] is a widely used screening tool to measure psychological distress. The K-10 is a short questionnaire composed of 10 items that investigate the frequency of psychological symptoms experienced by the individual in the last month, such as nervousness, sadness, tiredness, and feelings of hopelessness, for example, “During the last 30 days, about how often did you feel tired out for no good reason?” Each question is rated on a 5-point scale, ranging from “none of the time” to “all of the time.” Total scores range from 10 to 50, with higher scores indicating greater psychological distress (scores ≥30 suggest a high likelihood of a severe mental disorder).

The Multidimensional Psychological Flexibility Inventory (MPFI) [46] is a tool designed to assess psychological flexibility across multiple dimensions. It investigates how people adapt their thoughts and behaviors in response to changing situations and challenges. The MPFI focuses on various aspects of psychological flexibility. In particular, there are 6 scales for flexibility (acceptance, present moment awareness, self as context, defusion, values, and committed action) and 6 scales for inflexibility (experiential avoidance, lack of contact with the present moment, self as content, fusion, lack of contact with values, and inaction), according to the Hexaflex model [46]. For each of these dimensions, there are 5 items with responses ranging from 1 (“never true”) to 6 (“always true”).

PSS is a self-report questionnaire used to measure perceived stress. In particular, the objective is to determine the degree to which situations are perceived as stressful in a person’s daily life. Using 10 items rated on a 5-point Likert scale, this tool assesses participants’ thoughts and feelings over the past month regarding specific events, such as how often they felt unable to control important aspects of their lives. For each item, participants indicate the frequency on a scale from 0 (“never”) to 4 (“very often”).

SF-36 [29] is the most widely used general health measurement tool. It is a questionnaire divided into 8 sections: physical functioning (10 items), limitations due to physical health (4 items), limitations due to emotional problems (3 items), energy and fatigue (4 items), emotional well-being (5 items), social activities (2 items), pain (2 items), and perception of general health (36 items). For each dimension, the scores of the questions are coded, summed, and transformed into a scale ranging from 0 (worst health state) to 100 (best health state).

The platform adopted for the intervention allows for the recording of activity logs, enabling proper mapping of patients’ actions and experiences. This covers a range of logs, assessing whether the participant is properly exposed to the intervention protocol while recording use patterns (eg, session execution time, number of accesses, and use patterns of different features). Included among the variables considered are any missed sessions or interruptions. These data will be correlated with acceptability scores during the analysis phase. If a patient does not complete activities and fails to fill in specific questionnaires (leading to missing data), specific information on patients’ experiences and platform use will be collected during the scheduled postintervention interview sessions.

#### Phase 4: Follow-Up

The follow-up interview will be carried out 4 months after the conclusion of the SH+ process; will last approximately 20 minutes; and, subject to the patient’s consent, will be audio-recorded to allow subsequent analysis. The interviews are structured with ad hoc items specifically designed to capture key characteristics of the study and participants’ experiences. They are conducted by psychologists from the design team. During the qualitative interview, the patient will also be asked if someone supported them during the intervention, how easy it was to carry out the exercises, and general personal perceptions about the usability and real-world application of this app. Interviews will be conducted 4 months after the end of the intervention and will last approximately 20 minutes.

### Privacy and Data Management

At the time of recruitment, privacy documentation is available in line with Articles 13 and 14 of EU Regulation 2016/679 (General Data Protection Regulation), with specific focus on purposes and legal grounds of data processing, including information on how the personal data will be collected, the types of personal data collected, how the data will be managed, the retention period, the responsibilities of data controllers, and the rights of data subjects. Personal data are processed for specific research purposes within the scope of public interest tasks of the data controllers. Informed, freely given, voluntary, and explicit consent regarding the processing of special personal data (ie, data concerning health and data on self-reported behavioral habits in the area of lifestyle health) will be collected. Moreover, specific consent will be collected on the possibility of contacting the data subject via telephone to conduct research interviews. All data collected will be kept confidential, and data necessary for evaluating the study objectives will be pseudoanonymized before processing.

Access to personal or sensitive data is strictly limited to authorized IT specialists solely for the purpose of platform maintenance and in accordance with standard operating procedures and data protection protocols. App developers and platform hosts do not access personal or sensitive user data for any other purpose.

Copies of the information on the study and of the privacy policy will be issued to the participant and made available in a dedicated section of the app.

The study manager produces a report on the research and ensures that the data are reported responsibly and consistently. Personal data will neither be disclosed nor disseminated, except in anonymized or aggregated form for publication purposes. The transmission or dissemination of the data will take place exclusively in anonymous form, using only aggregated data that prevent any direct or indirect identification of the participants.

### Data Analysis

#### Overview

Preliminary data analysis is scheduled for early November 2024, while the final results will be available at the end of the study. The publication of the results will take place within 1 year after the conclusion of the study. Given the potential for dropout, which is commonly observed in digital interventions, and the sensitive nature of our sample population, missing data will be carefully addressed during the analysis phase. Where appropriate, multiple imputation methods will be applied to account for missing values and reduce potential bias. In addition, participants who drop out or fail to complete the follow-up assessments will be included in the analysis using an intention-to-treat approach, wherever feasible.

#### Quantitative Analysis

Statistical data processing will be conducted using the software R (version 4.0.0; R Foundation for Statistical Computing) [47], SPSS (IBM Corp) statistics [48], Stata (version 17) [49], and Jeffreys’s Amazing Statistics Program [50].

Categorical variables will be summarized using absolute frequencies and percentage distributions, while quantitative variables will be summarized using specific measures of central tendency and variability. Descriptive analyses will cover psychological variables (stress level, anxiety level, depression level, emotional regulation, psychological flexibility, coping strategies, well-being, and health status) as well as UX and usability variables. Relationships between variables will be analyzed primarily using ad hoc statistical tests, including the chi-square test, Fisher exact test, paired *t* test, Wilcoxon signed rank test, and sign test, depending on the assumptions met. These tests will help identify differences between the beginning and end of the course within the same study sample for the variables under investigation. In addition, univariate logistic or multinomial regression models will be presented. To account for potential confounding factors, multiple regression models will be proposed, adjusting the effects of explanatory variables on outcome variables for possible confounders. Statistical significance will be found for each analysis with a *P* value ≤.05*.* The McNemar test [51] and Cochran Q test [52] will also be used to evaluate paired qualitative data.

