#### Sample Size

This research project is designed as a POC study, where a limited sample is sufficient to achieve the intended aims. On the basis of calculation assuming a nonnormal distribution and using nonparametric statistics, a sample of 24 women with BC diagnoses is sufficient when applying a Bonferroni-corrected significance level (α=.025) to control for type I error and multiple comparisons. Nevertheless, to validate this estimate, the sample calculation was run with the Power Analysis and Sample Size 2021 (NCSS, LLC) and Stata (StataCorp LLC) programs. The resulting sample size is 41 participants, based on the following assumptions: a significance level (α) of .025, statistical power of 0.80 (to ensure sufficient sensitivity to type 2 error), a mean difference between groups (eg, pre- and postintervention questionnaires) of 1.00, an expected effect size (δ) of 0.50, and an SD of 2.00.

The chosen effect size (Cohen *d*=0.50) reflects a moderate change [31], which is consistent with previous digital mental health interventions in populations with psychological disorders [32]. This approach aligns with recommended practices in early-stage mHealth research, where the focus is on identifying potential signals of efficacy rather than definitive effect estimates [22]. Therefore, considering a 20% possible dropout [33], 50 women were estimated to need to be recruited to carry out the study. This approach is also coherent with previous studies adopting this type of methodology in the field of mHealth.

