#### Secondary Outcomes

The variables expressing the psychological well-being outcomes will be assessed by administering self-report questionnaires at the beginning (screening and week 0) and at the end (week 6) of the intervention (Textbox 2 provides a detailed overview of the questionnaire adopted). The end points to be measured include the scores of individual questionnaire items, the average scores of the questionnaires, and the differences between the average scores of the questionnaires at 2 survey times. In addition, the Perceived Stress Scale (PSS) [38] will be administered during a follow-up conducted 4 months after the study’s conclusion.

Both the clinical and usability tests will yield within-subject and between-subject comparison results.

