From a technical standpoint, collaboration with computer science experts will continue throughout the study to ensure the app is properly designed and maintained. We referred to internal usability studies and the previous co-design paper [24] as key examples to evaluate and refine the app’s functionalities before this pilot phase, but all new technical issues, such as bugs and glitches, will be monitored online throughout the development of the chatbot. This study aimed to identify and address any technical usability challenges before proceeding with a larger-scale trial. In other words, the findings from this feasibility study will inform decisions about scaling up the intervention or proceeding to a larger efficacy trial. Fundamental benchmarks will be based on key outcomes such as participant engagement rates, retention and dropout rates, significant changes in psychological variables (as mentioned earlier), and outcomes related to the acceptability and usability of the ALBA app, as measured by self-report questionnaires, along with the app’s functionality, including bug tracking. If these benchmarks are met, consideration will be given to moving forward with a larger, more definitive trial to assess the intervention’s efficacy. In addition, potential modifications to the intervention or trial design will be discussed, based on the results of this feasibility study, ensuring that the next phase could be better tailored to the needs of the target population in terms of content, functionality, and delivery methods.

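### The sample size assumes a Bonferroni-corrected α of .025 for two unnamed comparisons, but each analysis is judged at P≤.05 uncorrected, so the stated type I error control is not delivered.

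*Protocol article*

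**What the plan says.** Four places in the protocol article bear on this.

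- **Sample Size.** An initial figure of 24 women is given for nonparametric statistics, "when applying a Bonferroni-corrected significance level (α=.025) to control for type I error and multiple comparisons". A second calculation, which the plan adopts, again takes "a significance level (α) of .025, statistical power of 0.80", with an effect size of 0.50 and an SD of 2.00. It reports: "The resulting sample size is 41 participants". Allowing for 20% dropout, 50 are to be recruited.
- **Quantitative Analysis.** Several paired tests and regression models are listed for comparing the start and end of the course, followed by one decision rule: "Statistical significance will be found for each analysis with a *P* value ≤.05". No correction for multiplicity is named, and .025 does not appear.
- **Secondary Outcomes and Textbox 2.** "The end points to be measured include the scores of individual questionnaire items, the average scores of the questionnaires", together with differences between average scores. Textbox 2 lists six psychological questionnaires at week 6 that also have an earlier measurement: PSS, MPFI, GSE, ERQ and COPE-NVI-25 at week 0, and GHQ at screening.
- **Results.** Among the benchmarks for considering a larger trial are "significant changes in psychological variables (as mentioned earlier", without saying which variables or how many.

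**The concern.** An α of .025 described as Bonferroni-corrected is .05/2, so it protects two comparisons. The protocol never says which two. The analysis section then uses .05 for everything, so the error rate that sized the study is not the one that will decide what is called significant. The claim that type I error and multiple comparisons are controlled is therefore not carried into the analysis.

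A proof-of-concept study need not control familywise error, but this one says that it does. It also sets efficacy on psychological well-being as its secondary objective and uses significant psychological change as one input to the decision about a larger trial. There is no control group, so a chance improvement on one scale would have no comparison arm to expose it.

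**Working it through.** **Inputs.** From Sample Size: mean pre–post difference 1.00, SD 2.00, so d = 1.00/2.00 = 0.50; α = .025; power 0.80; 20% dropout. From Quantitative Analysis: threshold .05 per analysis. From Textbox 2: six psychological questionnaires with a before and a week-6 measurement. From Psychological Assessment: the item counts.

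**Step 1: reproduce the plan's figure.** Paired t test, noncentral t distribution, d = 0.50, power 0.80:

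- two-sided α = .025: n = 41 (power at 41 is 0.805), the plan's figure;
- one-sided α = .025, or two-sided α = .05: n = 34.

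The normal approximation at two-sided .025 is n = ((2.241 + 0.842)/0.50)² = 38.0, rounded up to 39; the t correction takes this to 41. So the plan's 41 is driven by a two-sided α of .025. At the threshold in the analysis section, 41 evaluable women give power of 0.878. With 50 recruited and 20% lost, 50 × 0.80 = 40 remain; power is then 0.793 at .025 and 0.869 at .05, which changes nothing material.

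**Step 2: chance of at least one false positive.** With no true change and k independent tests at level a, this is 1 − (1 − a)^k.

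| Tests | a = .025 | a = .05 |
|---|---|---|
| 2 | 1 − .975² = 4.9% | 1 − .95² = 9.75% |
| 6 | 1 − .975⁶ = 14.1% | 1 − .95⁶ = 26.5% |

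The six-test row takes one score per questionnaire. This is an assumption: the protocol describes the MPFI as 12 dimensions and defines no total.

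**Step 3: correlation between scores.** The documents give no correlations, so a range is assumed. In a simulation of six equally correlated normal statistics (100,000 draws), each judged at .05, the chance of at least one false positive is 24.0% at correlation 0.3, 20.4% at 0.5 and 16.5% at 0.7. All remain well above 5%.

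**Step 4: item scores, only if tested.** PSS 10 + MPFI 60 (12 dimensions × 5) + GSE 10 + ERQ 10 + COPE-NVI-25 25 + GHQ 12 = 127. Expected false positives at .05: 127 × .05 = 6.35. That expectation does not depend on correlation. The chance of at least one does: 99.9% under independence, but 97% to 53% at assumed correlations of 0.3 to 0.7.

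**Step 5: cost of covering all six scores.** Bonferroni gives .05/6 = .0083. The same inputs then need 52 evaluable women; power at 41 is 0.66.

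**The case against.** The best attempt to reconcile the two passages is to read .025 as one tail of a two-sided .05. It fails. The protocol calls the figure Bonferroni-corrected, and a one-sided .025 gives 34, not 41.

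The stronger objections concern the consequences, and much of them stands.

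- **Item-level testing.** A reader might infer that all 127 psychological items will be tested and that a false positive is nearly certain. The documents do not support this. Item scores are listed as end points to be measured, while the variables named in Quantitative Analysis are constructs such as stress or coping. Near certainty also needs weakly correlated items.
- **Usability items.** A reader might add the 33 items of the UES-SF, SUS and ITA BUS B. The planned tests are described as comparing the beginning and end of the course, and these instruments have no week 0 measurement. They are not counted here.
- **The decision on a larger trial.** A reader might infer that one chance P value would trigger it. The Results section lists several benchmarks, including engagement, retention, usability and app functionality, and meeting them leads only to consideration of a larger trial.
- **Context.** The primary outcomes are user experience and usability, psychological efficacy is secondary, and the Sample Size section speaks of looking for signals. Power is not harmed, since .05 is the more lenient threshold.
- **Choice among paired tests.** Leaving the exact rule to a fuller document is normal in a condensed article and is no part of this point.

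These arguments lower the stakes. They do not remove the contradiction, which lies within the article and does not depend on an unseen analysis plan.

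**Conclusion.** Wrong as written: the protocol claims a type I error control that its decision rule does not deliver. For the two comparisons that .025 implies, the chance of at least one false positive is 9.75% rather than 4.9%, assuming independence. For six psychological scores, one per questionnaire, it is about 26% if independent and about 16–24% at assumed correlations of 0.7–0.3. Applying .025 to all six would still give about 14% under independence, so the comparisons also need to be named. If items were tested, which the protocol does not state outright, about 6 of 127 would be expected to reach P≤.05 by chance.

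This should be fixed, since a stated error rate is incorrect and significance feeds one benchmark. It does not threaten the primary usability aims or the adequacy of 41 evaluable women.

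**What to change.** Choose one of two wordings.

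- **(a) Keep the correction.** In Sample Size and Quantitative Analysis, name the two comparisons that α = .025 covers and judge them at .025. The 41 evaluable women then stand at 80% power. Report all other scale scores as estimates with 95% confidence intervals and no claim of significance, and keep item scores descriptive. Which two comparisons to name is the investigators' choice.
- **(b) Drop the correction.** Remove the Bonferroni claim from Sample Size, call all psychological tests exploratory, and restate power at α = .05: about 88% with 41 evaluable at d = 0.50.

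In either case, reword the psychological benchmark in the Results section to match, using the named comparisons or estimates with confidence intervals.

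The cost is wording only, with no extra women, visits or data. The downside is that fewer nominally significant results can be claimed.
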